#### Phase 4: 32-contact surgical lead anchoring

After completion of lead programming testing, the lead will be permanently implanted and secured with appropriate anchoring, at its final vertebral level. A final X-ray check will be performed to ensure that the lead has been adequately secured and will not be subject to displacement, once the lead programming and the patient coverage are optimal [24, 25].

#### Phase 5: IPG implantation

Subjects, who succeed in the TCS SCS screening test (global pain VAS score decrease ≥ 50% after a 7-day period trial according to the French Health Authority guidelines), receive a Precision Spectra SCS System™ IPG. At this stage, subjects receive TCS during 2 months before the randomization to avoid any period-related bias due to the pain scar. After the 2 -month period, the subject is randomized to one of the six arms. After the crossover period, subjects choose their preferred modality for a follow-up period of 12 months. Subjects who fail the screening test are excluded from this study.

### Spinal cord stimulation programming modalities

#### Paraesthesia-based waveform using Illumina 3D™ Algorithm

Supported by Multiple Independent Current Control (MICC) hardware, Illumina3D™ is a model-based anatomically guided 3D Neural targeting programming algorithm, designed to precisely calculate anodic and cathodic current distribution at each lead contact. The resulting field shape (or Central Point of Stimulation) is then used as the target for the delivery of various waveforms, including paraesthesia-based stimulation waveform, BURST and HF using Illumina3D™ Algorithm (Fig. 2).

#### Tonic conventional stimulation

TCS patterns are tested thanks to patient cooperation, using various predetermined combinations, in order to achieve good pain coverage and validate the sweet spot location. TCS operates at frequency range of 10–100 Hz for every patient with pulse width of 10–500 μs and amplitude 0.1–25 mA. TCS significantly increases the spontaneous activity of neurons in the gracile nucleus, which are known to project to the primary somatosensory cortex in the brain. This increased spontaneous activation of the spinal nucleus may account for the sensation of paraesthesia that typically occurs during TCS [26].

#### Burst

BURST stimulation consists of closely spaced, high-frequency stimuli delivered to the spinal cord. The stimulus paradigm consists of a 40-Hz burst mode of constant-current stimuli with 5 spikes at 285–332 Hz per burst, pulse width of 10–500 μs, interspike intervals of 3 ms and amplitude corresponding to 50–70% of the sensitive threshold. The differences between TCS and BURST stimulations could be due to more selective modulation of the medial pain pathways by BURST stimulation, as evidenced by activation of the dorsal anterior cingulated cortex [27]. Recent literature supplies good evidence for the efficacy of BURST SCS in the treatment of FBSS with chronic neuropathic radiculopathy [14, 15, 17].

#### High frequency

While HF is generally operated with a range of 500 Hz to 10 kHz, new SCS systems have been developed and make it possible to deliver stimulation up to 10 kHz. The device allows delivery of HF stimulation from 650 to 1200 Hz with pulse width of 10–500 μs, and amplitude corresponding to 60–65% of the sensitive threshold. HF may offer several distinct benefits over TCS. The first would suggest that this therapy could address axial back pain more effectively, which often does not respond as well to traditional SCS. The second is based on the fact that HF, as BURST SCS, appears capable of delivering pain relief without inducing any paraesthesia. This last observation could have obvious benefits for patient acceptance of SCS therapy and could also simplify system implantation by avoiding intraoperative paraesthesia mapping, required to ensure proper lead positioning [28]. The efficacy of HF SCS is still debated in the literature [18, 19, 29, 30].

### Clinical assessments

Outcome measures selected for this trial are based on a review of the previous RCTs of SCS and consideration of IMMPACT recommendations [31]. The visit of randomization is M0 for the study period. Subjects are assessed prior to randomization (M0) and at 1-month, 2-month, 3-month, 6-month, 9-month and 15-month follow-up visits. Assessments are performed by appropriately trained and delegated study staff. The summary of data collection is presented in Table 1.

**Table 1 Tab1:** Multiwave study—summary of data collection

Study procedure	Enrollment visit	Implantation visit (inclusion)	M_0_ visit (randomization)	M_1_	M_2_	M_3_	M_6_	M_9_	M_15_
Patient information	x								
Informed consent form	x								
Inclusion and exclusion criteria	x	x							
Thoracolumbar X-rays	x	x							
Medical and surgical history (including TENS therapy)	x								
Analgesic treatments, concomitant medications and non-drug treatments	x	x	x	x	x	x	x	x	x
DN4 questionnaire (neuropathic pain)	x								
N3MT (NeuroMapping Tool) pain surface, intensities, paraesthesia coverage	x	x (pre/per/post-implantation)	x	x	x	x	x	x	x
Paraesthesia perception VAS		x (pre/post-implantation)	x	x	x	x	x	x	x
Global, back and leg pain VAS	x	x	x	x	x	x	x	x	x
Patient diary (complete within 1 week prior to visit)		x	x	x	x	x	x	x	x
Nasal *Staphylococcus aureus* decolonization (2 days prior to visit till 2 days after)		x							
Phone call*		x	x	x	x	x	x	x	x
EUROQOL 5-Dimensions (EQ5D)	x	x	x	x	x	x	x	x	x
Oswestry Disability Index (ODI)	x	x	x	x	x	x	x	x	x
Hospital Anxiety and Depression Scale (HADS)	x	x	x	x	x	x	x	x	x
Patient Satisfaction/Patient Global Impression of Change (PGIC)			x	x	x	x	x	x	x
Programming session		x	x	x	x	x	x	x	x
Adverse event/severe adverse event	x	x	x	x	x	x	x	x	x

*Phone call: 1 week prior to the planned visit (patient diary)

### Primary outcome

The primary outcome is the variation of average global VAS score, assessed over a 5-day pain diary, between baseline (randomization, M0) and after each treatment period [31]. Patients record their global, back and leg pain using a (paper) pain diary once a day, for a 5-day period within 1 week prior to each scheduled study visit.

### Secondary outcomes

Secondary outcomes are variation of leg and back pain relief, as measured by VAS [32]; proportion of responders in each group, as responder defined by ≥ 50% reduction of pain; variation of functional disability, as measured by the Oswestry Disability Index Questionnaire (ODI) [33]; variation of quality of life, as measured by EuroQol-5 Dimension (EQ5D) [34]; variation of anxiety and depression, as measured by Hospital Anxiety and Depression Scale (HADS) [35]; variation of paraesthesia, as measured by VAS; the patient satisfaction, as measured by Patient Global Impression of Change (PGIC) [36]; and adverse events, device deficiencies and concomitant treatments.

Further, pain surface, pain intensities and paraesthesia surface are quantified with objective quantitative measurements (Neuro-Pain Software) to compare Global Pain Surface reduction, pain intensity reduction and paraesthesia coverage surface between arms groups [24, 25].

### Process measures

At the screening and baseline visits, the following additional pieces of information are collected: subject demographics (for example, age, gender) and a neuropathic pain assessment by clinician-administered diagnostic questionnaire (e.g. Douleur Neuropathique en 4 questions) to discriminate neuropathic pain components of low back pain [37], surgical and medical history, radiological assessments of thoracolumbar (X-rays) and Nasal *Staphylococcus aureus* decolonization (2 days prior to visit until 2 days after). Subjects who proceed to device implantation have the following information collected: pain/paraesthesia by tactile interface mapping data (NeuroMapping Tools software), lead programming parameter settings, electrode location and device implant information. The NeuroMapping tool is a validated quantitative tactile interface allowing the patient to delineate painful zones in the back and legs and to precisely map objective changes in pain coverage and SCS performance [24, 25].

Unscheduled patient visits could occur between scheduled study follow-up visits due to patient discontinuation from the study or device reprogramming and management of any complication.

### Sample size and power calculations

To calculate the sample size of our study, we started by focusing on the pairwise comparison of HF stimulation and TCS (using a Wilcoxon signed-rank test) while taking into account the Bonferroni correction. BURST and HF stimulation did not show any differences in the literature [21], which was lacking during the development of our study. However, studies comparing HF stimulation and TCS were available, and the paper by Kapural et al. [38] was the largest study comparing these two modalities. In their research, they found a difference of − 1.7/10 95% CI = [− 2.6; − 0.8] points in pain VAS between the two independent groups of HF stimulation and TCS. We decided to proceed with a minimum change of 2.0/10 points as it was found to be the minimum clinically significant difference in pain VAS [32]. To estimate the standard deviation of the difference between treatments while taking into account our crossover design, we needed to estimate intra-subject correlation. It was recommended in the Cochrane handbook to impute missing intra-subject correlation by (SD_1_^2^ + SD_2_^2^ − SD^2^_change_)/(2 × SD_1_ × SD_2_) where SD_1_ = 3.0 and SD_2_ = 2.5 are the standard deviations of the two time points/treatments. Based on data from Kapural et al. [38], we estimated intra-subject correlation of 0.52. We have chosen a correlation of 0.60 as we thought that it would be larger for real paired samples.

Assuming a mean difference of 2 points, a standard deviation of the difference of 2.5 (the square root of SD_1_^2^ + SD_2_^2^ − 2 × corr × SD_1_ × SD_2_ = the square root of 3.0^2^ + 2.5^2^–2 × 0.6 × 3.0 × 2.5), a significance level of 0.0167 (Bonferroni correction) and a power of 0.8, a total sample size of 23 is required and stepped up to 24 in order to ensure a balanced number of subjects per arm. To consider 15% dropout, we decided to include 28 patients.

We also conducted a simulation of 100,000 samples to conduct Friedman tests using the following hypotheses: A difference of 2.0 points between TCS and HF stimulation (5.0/10 (SD = 2.5) vs 3.0/10 (SD = 3.0)), no difference between BURST and HF stimulation (3.0/10 (SD = 3.0) vs 3.0/10 (SD = 3.0)), a correlation of 0.60 between every two treatments (included in the multivariate normal distribution covariance matrix) and a significance level of 0.05. We obtain an estimated power of 96.1% for 28 patients and 90.9% for 23 patients, for detecting the hypothesized difference between the three groups.

### Procedures to minimize bias

To minimize selection bias, randomization sequence is prepared using a random selection programme developed under SAS V9.3. Randomization numbers are assigned in strict sequence, i.e., when a subject is confirmed eligible for randomization, the next unassigned randomization number in the randomization sequence is given. Randomization allocation is hidden from the clinician and subject, using a centralized automatic web-based data management system (https://www.dirc-hugo-online.org/csonline) dedicated to the study and accessible to investigators by username and personal password. Once given, the randomization assignment for the subject cannot be changed. Early departure from the study does not give rise to replacement or reassignment of the rank of inclusion.

Due to the paraesthesia generated by the TCS waveform, the study can be blinded only with HF and BURST stimulation modes. Indeed, for these two types of stimulation, the first step consists in increasing stimulation amplitude until the patient starts feeling paraesthesia. At this amplitude, the programme (combining anodes and cathodes) with the optimal coverage of pain surface is selected. Once the optimal programme is chosen, the minimal threshold allowing paraesthesia perception is identified. Based on it, the patient device remote control is adapted so that patients can modulate stimulation intensity (BURST or HF) only from 20 to 50% of this reference amplitude. By following these recommendations of the manufacturer, patients do not feel paraesthesia with BURST and HF stimulations, which ensures the patient-blinding trial. Double-blind is ensured by conducting patient evaluation and SCS programming by two different agents. Unblinding is made according to the sponsor site procedure. The randomization list is held by the Pharmacy of the CHU of Poitiers.

### Statistical analysis

Categorical variables will be described by numbers and percentages while quantitative variables will be described by the mean and its confidence interval or median and interquartile range based on the skewness of the variable. The study sample will be described by age, gender, BMI, duration between pain appearance and device implantation, number of spinal surgeries and type of pain (neuropathic/mechanical). The primary hypothesis of the difference between TCS, BURST and HF will be verified using the Friedman test or repeated measures ANOVA depending on the normality of the global pain VAS (average VAS over the 5-day diary period). Shapiro-Wilk test will be used to test for non-normality of distributions. In case the Friedman test indicates significance, a post hoc test using the procedure described by Conover [39] and the Bonferroni *p* value adjustment method will be conducted for pairwise comparisons. Ordinal outcomes will be compared between groups using the same previously described procedure. Quantitative normally distributed endpoints will be compared between groups using repeated measures ANOVA. Pairwise comparisons will be conducted after the repeated measures ANOVA indicate significance. Binary outcomes will be compared using the Cochran Q test and a McNemar test will be conducted for pairwise comparison after the Cochran Q test rejects the null hypothesis.

After the end of the crossover design, patients will choose a preferred waveform and will be followed for 1 year. The proportions of waveform preference will be compared using a chi-square goodness of fit test. The categorical variables will be compared between visits M6, M9 and M15 and baseline using the McNemar test while the continuous variables will be compared between baseline and the post crossover visits using the paired *t* test or Wilcoxon signed-rank test depending on the variables’ distribution. All comparisons will be two-sided with a level of significance of 0.05. Missing data will be described. Patients with missing data on the primary outcome will be excluded from the analysis. The blind analysis is aimed to be conducted in per-protocol analysis. A robustness analysis including all available data will be conducted on the primary outcome using a Skillings-Mack Test. R software will be used for statistical analysis.

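### A normality test on the raw pain scores, rather than on the within-patient differences, decides whether the primary test is Friedman or repeated measures ANOVA

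*Protocol article*

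**What the plan says.** The Statistical analysis section says that the primary hypothesis will be tested by Friedman or by repeated measures ANOVA, "depending on the normality of the global pain VAS (average VAS over the 5-day diary period"). It adds that the "Shapiro-Wilk test will be used to test for non-normality of distributions". It gives no level for that test. It does not say whether the test is applied to pooled scores or to each waveform, and it does not mention residuals or differences.

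The Primary outcome section defines the endpoint as a change: "The primary outcome is the variation of average global VAS score, assessed over a 5-day pain diary, between baseline (randomization, M0") and the end of each treatment period.

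The Sample size section sizes the trial on means: "Assuming a mean difference of 2 points, a standard deviation of the difference of 2.5". A further simulation there gives power for the Friedman test only: 96.1% with 28 patients and 90.9% with 23. It assumes multivariate normal scores, TCS 5.0 (SD 2.5), HF and BURST each 3.0 (SD 3.0), and correlation 0.60. The inclusion criteria bound the VAS at 0 and 100 mm.

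**The concern.** This is a stated rule, not a detail left to an analysis plan that is not shown. It raises two problems.

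First, the two branches answer different questions. Repeated measures ANOVA compares mean VAS. Friedman compares within-patient ranks. A preliminary test on 24 to 28 patients decides which question becomes the primary one, and in some data sets that also decides whether the result is significant.

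Second, the gate looks at the marginal distribution of the scores. ANOVA on a crossover needs roughly normal within-patient errors. Scores piled up near zero under an effective waveform, or skewed pain levels across patients, can fail Shapiro-Wilk while the contrasts are well behaved. The gate can also pass when the contrasts are badly behaved.

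**Working it through.** **1. What the two tests depend on.** Add any constant to all three scores of one patient, for example by subtracting that patient's M0 value. The within-patient ranks are unchanged, so Friedman is unchanged. The patient effect absorbs the constant, so the ANOVA F is unchanged. The distribution of the scores does change, so Shapiro-Wilk on the scores can change. The gate responds to a feature that neither test uses.

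**2. The plan's own figures.** SD of the difference = √(3.0² + 2.5² − 2 × 0.6 × 3.0 × 2.5) = √(9 + 6.25 − 9) = 2.5, as stated. Friedman power from 100,000 multivariate normal samples with the stated inputs is 96.2% (n=28) and 91.1% (n=23), against the stated 96.1% and 90.9%. The plan's figures reproduce.

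**3. The floor.** Under the planning values zero lies (0 − 3.0)/3.0 = −1 SD from the HF and BURST means, so Φ(−1) ≈ 16% of their scores would fall below the scale. Real scores cannot, so the raw distribution must depart from normal in some way. The documents do not say how, so I used three models:
- unbounded normal, as in the plan's simulation;
- the same values clipped to 0–10;
- beta margins that keep the stated means and SDs on 0–10, with correlation about 0.6.

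Clipping alters the inputs. The HF and BURST mean becomes 3.24 and the SD falls from 3.0 to 2.57, so a nominal 2.0-point effect is 5.00 − 3.24 = 1.76 points.

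**4. Results at the planned effect, n=24.** Assumptions that the documents do not state: Shapiro-Wilk at 0.05, and rejection in any one waveform leads to Friedman. Each scenario has 5,000–6,000 trials.

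| Score model | Raw scores rejected (any of 3 waveforms) | Differences rejected (any of 3) | Residuals rejected | Friedman power | ANOVA power | Two-stage power |
|---|---|---|---|---|---|---|
| Unbounded normal | 15% | 15% | 3% | 93.4% | 98.2% | 97.5% |
| Clipped | 63% | 16% | 4% | 91.9% | 97.3% | 94.6% |
| Beta | 99% | 32% | 9% | 95.4% | 97.6% | 95.5% |

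The HF–TCS difference alone, the contrast on which the trial is sized, is rejected in about 5–7% of trials at the planned and smaller effects. If Shapiro-Wilk is applied to the pooled scores instead, the clipped case rejects in 80%. At n=28 the clipped range is 72–88%.

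**5. Smaller effects, n=24.**
- Nominal 1.5 points, clipped: Friedman 69–70%, ANOVA 79%, two-stage 73–74%.
- 1.5 points, beta: Friedman 81–84%, ANOVA 79–80%.
- 1.0 point, beta: Friedman 56–60%, ANOVA 43–49%.
- The two tests disagree on significance in about 15–17% of trials at a nominal 1.5 points under normal or clipped scores. At the planned effect they disagree in 4–7%.

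**6. Type I error of the two-stage rule, equal means.** It is 4.9–5.3% under normal, clipped or skewed-patient scores. With beta margins and equal means but SDs of 2.5, 3.0 and 3.0, it is 8.6% (n=24) and 9.2% (n=28), against 4.9–5.0% for ANOVA. The gate sends nearly every such trial to Friedman, which detects the unequal shapes.

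**7. A case the gate misses.** With heavy-tailed within-patient errors (t, 3 df, n=24), Friedman is the stronger test at the planned effect: 99.2% against 96.8%. The gate nevertheless chooses ANOVA in about 69–77% of trials.

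**The case against.** The rule is written down in advance, is mechanical and does not look at the treatment contrast. It leaves no room to pick the test that gives the better p value, beyond the unstated level and unit of the Shapiro-Wilk test. At the planned effect two-stage power stays near 95% or above, and the sample size section already powers the Friedman branch. All of this stands.

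Four stronger readings are tempting, and the documents do not support them.
- *The gate tends to select the weaker test.* Friedman loses about 5 points of power at the planned effect under normal or clipped scores. Under the plan's own unbounded model, however, the gate seldom fires. Under beta margins Friedman is as strong or stronger below 2.0 points.
- *The gate produces false positives.* Under normal or clipped scores it does not. The 8–9% under unequal shapes counts as an error only if the hypothesis is about means, and the plan leaves that open.
- *The branches carry different multiplicity rules.* The article names Bonferroni after Friedman and does not repeat it for ANOVA, but its sample size section plans pairwise tests at "a significance level of 0.0167 (Bonferroni correction) and a power of 0.8, a total sample size of 23 is required". Silence in a condensed article is not a different rule.
- *The Wilcoxon sizing shows the same fault.* The statement that "we started by focusing on the pairwise comparison of HF stimulation and TCS (using a Wilcoxon signed-rank test") concerns how the number of patients was reached. It says nothing about the normality gate.

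The like-for-like comparison also limits the claim about differences. Under beta margins at least one of the three differences fails in 32% of trials, so they are better behaved than the raw scores but not always normal.

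**Conclusion.** The concern holds in a limited form. The protocol leaves the primary test and its hypothesis to a Shapiro-Wilk result on a quantity that does not determine whether ANOVA is valid. On the plan's own means and SDs, the raw scores would often fail that check although the HF–TCS contrast is close to normal.

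The cost is an indefinite primary hypothesis and a conclusion that can turn on the branch taken, in roughly one trial in six at effects somewhat below 2.0 points under normal or clipped scores. It is not a general loss of power or a general excess of false positives. The sizes rest on the assumed 0.05 level, the any-waveform rule and the assumed shape of the bounded scores. That the check is on the wrong quantity rests on none of these.

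**What to change.** Delete the normality gate for the primary outcome and name one primary within-patient analysis. A means-based one is the natural choice: repeated measures ANOVA, or an equivalent mixed model, on the 5-day mean global VAS, with Bonferroni-adjusted pairwise mean differences and confidence intervals. These can be set directly against the 2.0-point difference used for sizing. A mixed model is not required. Naming Friedman as primary would also remove the ambiguity, but the hypothesis should then be stated in terms of ranks.

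Report Friedman as a fixed sensitivity analysis whatever Shapiro-Wilk shows. If a normality check is kept for description, apply it to residuals or differences.

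If ANOVA becomes primary, restate the power for it. With the stated inputs it is 97.6% (n=23), 98.2% (n=24) and 99.3% (n=28), so the sample size does not change.

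The cost is a dated change to the protocol and analysis plan, made before the treatment comparison is run, plus one revised power statement. No visit, patient or data item is affected. The downside is reliance on approximately normal within-patient differences, which the Friedman sensitivity analysis covers.

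### The Friedman-branch post hoc (Conover plus Bonferroni) ties the BURST–HF error rate to where TCS lies and gives up power; pair-specific tests behind the omnibus gate would do better, stated as one rule for both branches

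*Protocol article*

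**What the plan says.** The Statistical analysis section of the protocol article compares the three waveforms on global pain VAS by a Friedman test or a repeated measures ANOVA, depending on normality.

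- **Friedman branch:** "In case the Friedman test indicates significance, a post hoc test using the procedure described by Conover [39", with Bonferroni-adjusted p values for the pairs.
- **ANOVA branch:** "Pairwise comparisons will be conducted after the repeated measures ANOVA indicate significance". No pairwise test and no adjustment are named.
- **General level:** "All comparisons will be two-sided with a level of significance of 0.05".

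The section on sample size and power sizes the HF–TCS pair "using a Wilcoxon signed-rank test", at "a significance level of 0.0167 (Bonferroni correction) and a power of 0.8". It concludes that "a total sample size of 23 is required and stepped up to 24", and then: "To consider 15% dropout, we decided to include 28 patients". A separate simulation of the Friedman test assumes TCS at 5.0 and BURST and HF both at 3.0.

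**The concern.** The pairwise test fixed for the Friedman branch is not the one the trial was sized on, and it has a property that matters here. Conover's statistic ranks all three waveforms within each patient and uses one error term pooled over them. The chance of a false BURST–HF difference therefore depends on how far TCS lies from the other two, although TCS is not part of that comparison. The article's section on minimising bias and its Discussion both say that BURST–HF is the only comparison that can be blinded.

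With exactly three treatments, an omnibus gate followed by pairwise tests that each hold their own 5% level already controls the family-wise error. Two true pairwise nulls imply the third, so the closed family contains only the global null and the three pairs. Conover's test does not hold its own level for BURST–HF, so the plan relies on Bonferroni to make up for that. The result is lower power on the pair the trial was sized for.

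**Working it through.** **Inputs, all from the section on sample size and power.** Means are TCS 5.0, BURST 3.0, HF 3.0; SDs are 2.5, 3.0, 3.0; the correlation is 0.60 for every pair; n is 23, 24 or 28; omnibus alpha is 0.05 and the Bonferroni level 0.05/3 = 0.0167.

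**1. The plan's own figures.**
- SD of the difference: √(3.0² + 2.5² − 2×0.6×3.0×2.5) = √(9 + 6.25 − 9) = √6.25 = 2.5. Standardised effect: 2/2.5 = 0.8.
- Paired t test at 0.05/3, with n scaled by the minimum Wilcoxon efficiency of 0.864: 23×0.864 = 19.87 gives power 0.815; 22×0.864 = 19.01 gives 0.792. So n=23 reproduces.
- Simulated Friedman power is 96.0% at n=28 and 91.0% at n=23, against 96.1% and 90.9% stated.

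**2. Why the Conover error depends on TCS.** For k=3 without ties the statistic is

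t = |Rᵢ − Rⱼ| / √{2(nA − ΣR²)/[(n−1)(k−1)]}, with A = 14n (each patient contributes 1+4+9) and (n−1)(k−1) degrees of freedom.

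The limiting case shows the mechanism. Suppose TCS is ranked worst by every patient and BURST and HF are equal. The rank sums are then 3n, 1.5n and 1.5n on average:
- nA − ΣR² = 14n² − (9 + 2.25 + 2.25)n² = 0.5n².
- Estimated variance of the BURST–HF rank-sum difference: 2×0.5n²/[2(n−1)] = n²/[2(n−1)]. At n=28 this is 784/54 = 14.5.
- True variance: each patient contributes +1 or −1, so it is n = 28.

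The pooled term is about half of what it should be.

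**3. Operating characteristics** (multivariate normal, 20,000 to 100,000 simulated trials per setting, every pairwise test only after Friedman p<0.05):

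| n | Pairwise rule | TCS–HF power | Both TCS contrasts | False BURST–HF |
|---|---|---|---|---|
| 24 | Conover + Bonferroni (plan) | 80.5% | 70.0% | 2.6% |
| 24 | Conover at 0.05 | 88.6% | 84.2% | 7.4% |
| 24 | Signed-rank at 0.05 | 90.8% | 88.6% | 4.7% |
| 28 | Conover + Bonferroni (plan) | 87.0% | 79.0% | 2.5–2.7% |
| 28 | Conover at 0.05 | 92.7% | 89.5% | 7.0% |
| 28 | Signed-rank at 0.05 | 94.8% | 93.5% | 4.7–4.8% |

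**4. Splitting the gain for TCS–HF, removing Bonferroni first.** At n=24: 88.6 − 80.5 = 8.1 points from Bonferroni, then 90.8 − 88.6 = 2.2 from replacing Conover. At n=28: 92.7 − 87.0 = 5.7, then 94.8 − 92.7 = 2.1.

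**5. A larger TCS gap (4 points, n=28).** False BURST–HF findings are 5.7% with Conover plus Bonferroni, 11.8% with Conover at 0.05, and 4.7–4.8% with the gated signed-rank test.

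**6. Global null.** The family-wise error of the gated signed-rank procedure is 4.2–4.4%. In the ANOVA branch, gated paired t tests at 0.05 give 5.0–5.2% for BURST–HF when only TCS differs.

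**The case against.** The strongest defence is that the plan contains no failure on its own terms. Conover with Bonferroni yields 80–81% power for TCS–HF at n=24, matching the intended 80%, and a BURST–HF error below 3% in the planned scenario. An adjusted post hoc test after an omnibus test is conventional, and the Bonferroni level is the one used for sizing. This stands: the trial is not underpowered for its sized pair, and the point is an improvement rather than the repair of an invalid result.

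Three stronger readings are tempting and are not supported.

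- A reader might infer that Bonferroni behind the gate is simply wasted. It is not while Conover is kept: it brings BURST–HF false positives down from about 7% to about 2.6%. The closed-testing argument needs pairwise tests that hold their own level, and Conover's does not for this pair.
- A reader might infer that the ANOVA branch applies a different, unadjusted rule. The article names no test and no adjustment there; the full protocol or an analysis plan may settle it.
- A reader might cite very large TCS gaps, where Conover plus Bonferroni approaches 9% at n=28. An 8-point gap would put TCS at 3 + 8 = 11 on a 10-point scale, so that setting carries no weight. The 4-point gap is possible, but it is twice the planned effect.

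**Conclusion.** The point holds as a worthwhile, inexpensive improvement. Replacing Conover and Bonferroni together by gated pair-specific tests adds about 10 points of TCS–HF power at n=24 and about 8 at n=28. For winning both TCS contrasts it adds about 19 points (88.6 − 70.0) and about 14 (93.5 − 79.0). Family-wise error stays at most about 0.05, and the BURST–HF error no longer depends materially on TCS. Not all of this is due to Bonferroni: removed first, it accounts for about 8 of the 10 points at n=24, and the change of test for about 2.

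The figures rest on the plan's normal model, SDs and common correlation of 0.60, and on complete data for the stated n. The signed-rank test also assumes that the paired differences are symmetric under the null. Using paired t tests in the ANOVA branch is part of the proposal, since the article names none.

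**What to change.** For the primary outcome, state one rule covering both branches:

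1. Run the omnibus test at two-sided 0.05.
2. If it is significant, test each of the three pairs at two-sided 0.05 using only that pair's data: Wilcoxon signed-rank after Friedman, paired t after ANOVA.
3. Cite closed testing for three treatments as the reason no further adjustment is needed.

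Drop Conover and Bonferroni together. Do not drop Bonferroni alone. Restate the planned pairwise power for the gated procedure (about 91% at n=24 and 95% at n=28 for TCS–HF under the plan's assumptions), and fix the wording before the crossover data are analysed.

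The cost is a few sentences in the analysis plan and no patients. The disclosed downside is that the chance of a false BURST–HF finding rises from about 2.6% to about 4.7% in the planned scenario, still within 5%.
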